# HELP — Heidelberg decision aid for lung cancer patients: a randomized controlled clinical trial

**DOI:** 10.1186/s13063-023-07365-2

**Published:** 2023-05-25

**Keywords:** Lung cancer, Shared decision-making, Decision aid, Decision coaching

## Abstract

**Background:**

Shared decision-making (SDM), which increases the patient’s well-being, adherence, and success of treatment, is becoming increasingly important in medicine and especially in oncology. To empower patients to participate more actively in consultations with their physicians decision aids have been developed. In non-curative settings, such as the treatment of advanced lung cancer, decisions differ substantially from the curative setting, as uncertain gains in terms of survival outcomes and quality of life have to be weighed against the severe side effects of treatment regimens. There is still a lack of tools developed and implemented for such specific settings in cancer therapy that support shared decision-making. The aim of our study is to evaluate the effectiveness of the HELP decision aid.

**Methods:**

The HELP-study is designed as a randomized, controlled, open monocenter trial with two parallel groups. The intervention consists of the use of the HELP decision aid brochure, accompanied by a decision coaching session. The primary endpoint is clarity of personal attitude as operationalized by the Decisional Conflict Scale (DCS) after the decision coaching. Randomization will be performed as stratified block randomization according to the characteristic of preferred decision-making at baseline with a 1:1 allocation.

The participants in the control group get usual care, i.e., the doctor-patient conversation takes place without preliminary coaching and deliberation about their preferences and goals.

**Discussion:**

Developing decision aids (DA) for (lung) cancer patients with limited prognosis should empower patients to address these aspects and include information about “Best Supportive Care” as a treatment option. Using and implementing the decision aid HELP can not only give patients the possibility to include their personal wishes and values in the decision-making process, but also raise the awareness of shared decision-making itself among these patients and their physicians.

**Trial registration:**

German Clinical Trial Register DRKS00028023. Registered on 8 February 2022.

## Introduction

### Background and rationale {6a}

Shared decision-making (SDM) is becoming increasingly important in medicine and especially in oncology [1–5]. In SDM patients and caregivers discuss possible treatment options and patient preferences before making a decision together. When medical decisions have significant consequences for the patient’s future life, SDM increases the patient’s well-being, adherence to, and success of treatment [1, 6]. Particularly challenging in this context are the constantly evolving therapeutic algorithms associated with new treatment options that often only show marginal benefits and have to be balanced with end-of-life decision-making.

Decisions in the course of treatment are influenced by the doctor-patient relationship [7, 8]. This can tend to be paternalistic, i.e., the physician in his role as an expert either assumes responsibility and decision-making for the patient or the patient wishes him to do so. The model of shared decision-making, in which the physician and patient decide together on the basis of the available information and the patient’s preferences, has positive effects for patients and professionals [5]. However, it can only be applied if both professionals and patients are willing to take the patient’s preferences into account and make the decision together. Often, patients do not perceive the decision-making situations in the course of the disease as such and, in view of their situation, speak of an “absence of alternatives” to the form of therapy/treatment suggested by the professionals. Under certain circumstances, the diagnosis may give rise to a feeling of powerlessness and loss of control on the part of the patient. Shared decision-making therefore does not always take place and, as a result, the patient’s values and goals are not considered during the course of treatment. This can result in a poorer quality of life, over- or under-provision of care, reduced adherence to treatment, and increased stress for patients and hospital staff [9–11].

To empower patients to participate more actively in consultations with their physicians, decision aids have been developed [6, 12, 13]. Decision aids provide support for the individualized weighing of different decision options by presenting the benefits and risks of the measures under consideration in an evidence-based and generally understandable manner.

#### Existing knowledge

Patients wish more and more to participate in medical decision-making. This wish has increased steadily over the past 30 years. In 22 of the studies published from 2000 to 2012 on decision-making in cancer treatment, 85% of patients expressed a need to participate in medical decisions during their treatment process (vs. 62.5% in studies published up to 2000) [5].

Cancer patients often have unmet needs for information and communication about the disease, its course and prognosis, treatment alternatives, and side effects of therapy besides the above-mentioned strong desire to actively participate in treatment decisions [14, 15]. Patients who have a decision aid, on the other hand, feel better informed, are more aware of their own values, and participate more actively in the decision-making process [6, 12]. Compared with “usual care,” they also develop better coping strategies during the course of the disease, report fewer worries and fears, have more concrete assessments of the probabilities of therapeutic success and side effects, and show greater satisfaction with the therapeutic decisions [1]. Especially in oncology, decision aids are of particular relevance due to the severity of the disease and the importance of the decisions for the further course of life.

#### Need for a trial

Decisions taken in non-curative settings differ substantially from those taken in curative settings, as uncertain gains in terms of survival outcomes and quality of life have to be weighed against severe side effects of treatment regimens. There is still a lack of tools developed and implemented for specific settings in cancer therapy that support shared decision-making. By using the newly developed decision aid HELP accompanied by the decision coaching, lung cancer patients can become aware of their wishes, preferences, and needs with regard to treatment decisions. The aim of our study is to evaluate the effectiveness of the Help decision intervention and add evidence on decision aids in the context of incurable lung cancer.

### Objectives {7}

The aim of HELP is to promote patient autonomy and competence and facilitate shared decision-making in the context of treatment decisions for lung cancer patients. Patients who had decision coaching with the decision aid HELP are expected to show more clarity in their personal attitude concerning the treatment decision and feel better prepared for and more involved in the decision. The sum score of the dimension “clarity of personal attitude” in the Decisional Conflict Scale (DCS) was therefore chosen as a primary outcome.

Secondary outcomes are the effects of the HELP intervention on patients’ self-efficacy assessed via the Decision Self-Efficacy Scale, their perceived preparation for and involvement in treatment decision-making (Preparation for Decision-Making Scale (PDMS-D) and Patient Involvement in Care Scale (PICS)) and patients’ emotional state (EQ-5D-5L and Hospital Anxiety and Depression Scale (HADS-D)).

### Trial design {8}

The HELP-study is designed as a randomized, controlled, open monocenter, two-arm superiority trial with two parallel groups and a primary endpoint of “clarity of personal attitude” as operationalized by the Decisional Conflict Scale (DCS) which will be collected before the decision event. Following the assumptions that the HELP intervention strengthens patient autonomy and their clarity of personal values in relation to the treatment decision, the described design of the two-arm, parallel goups, superiority trials was chosen. Since it can be assumed that the effect of the HELP intervention will differ depending on the participant’s decision style, stratified randomization according to the decision type was chosen in order to take this aspect into account in the group comparisons of the outcome analyses. Therefore, randomization will be performed as stratified block randomization according to the characteristic of preferred decision-making at baseline with a 1:1 allocation.

## Methods: participants, interventions, and outcomes

### Study setting {9}

HELP will be conducted at the Department of Thoracic Oncology, University Hospital Heidelberg, which is one of the largest lung cancer centers in Germany. Here, about 600 patients are newly diagnosed with metastatic lung cancer every year.

### Eligibility criteria {10}

The patients involved in the study are facing a treatment decision due to a newly diagnosed lung cancer or due to a disease progression.

Inclusion criteria for patients:At least 18 years old;Able to give consent;Good German language skills;Diagnosis of incurable lung cancer (stage IV) and stage IIIb and IIIc; andWillingness to participate in the study.

Exclusion criteria for patients:Younger than 18;Insufficient knowledge of German;In a health condition that does not permit conversation due to a vital threat;Limitations in cognitive function; andUnable to give consent.

#### Decision coaches

The decision coaches are nursing professionals and psychologists who are trained in decision support and play a supporting, but neutral role in the decision. As the training for decision coaches and the conversation guide are standardized, variations in the decision coaching conversations should be kept to a minimum.

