### Sample size {14}

A clinically relevant difference of 10 points in the primary outcome between the two treatment groups was assumed to show a sufficient clinical difference for case planning. In addition, the standard deviation was estimated to be 20.6 from the literature [12]. Under these assumptions, *n*=71 patients per group are needed to demonstrate the assumed difference between the two groups at a two-sided significance level of 5% with a power of 80% using a Mann-Whitney *U* test. The calculation was performed by means of 100,000 simulation runs using the case number software PASS v 16.0.4. Taking into account a dropout rate of approx. 20%, 71/(1–0.20)=89 patients per group are included. These results in a total number of cases of *n*=178 patients are to be included in the study.

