## Statistical methods

### Statistical methods for primary and secondary outcomes {20a}

A descriptive analysis of all collected patient information and data (as well as the scales that can be formed from the instruments) is performed: mean, standard deviation, median, minimum, and maximum, for continuous variables and absolute and relative frequencies for categorical variables.

For all (primary and secondary) analyses, the intervention arm (HELP intervention: decision coaching and decision aid) will be compared against the control arm (standard care/decision situation). The primary outcome measure is the sum score of the clarity of personal attitude dimension of the Decisional Conflict Scale (DCS). In addition to the descriptive evaluation, it will be analyzed by group comparisons (non-parametric comparison: van Elteren test) between the two study groups in which the stratification of randomization is considered.

For the sum scores and scales of the secondary outcomes, group comparisons (taking stratification into account) are also performed in order to detect significant differences. Depending on the group, the Cochran-Mantel-Haenszel test, the van Elteren test, or an analysis of covariance are used.

Results are reported along with descriptive *p*-values and 95% confidence intervals. *P*-values will be reported to four decimal places with *p*-values less than 0,05 considered statistically significant. Analysis is performed using statistical software SPSS (version 27, IBM) or R (version 4.0. http://r-pro-ject.org) (Table 2).

**Table 2 Tab2:** Variables, measures, and methods of analysis

Variable/outcome	Hypothesis	Outcome measure	Methods of analysis
**1) Primary**	Intervention improved outcome in comparison to the control group		
Clarity of personal attitude/values clarity		Values clarity subscore of Decisional Conflict Scale (DCS-D)	van-Elteren-test

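### The sample size and primary test treat coached patients as independent although their scores are nested within decision coach, so a claim about HELP coaching in general rests on an unchecked assumption of negligible coach differences

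*Protocol article*

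**What the plan says.** Under Eligibility criteria {10}, Decision coaches, the article says that "The decision coaches are nursing professionals and psychologists who are trained in decision support and play a supporting, but neutral role in the decision". It adds that, because training and conversation guide are standardised, "variations in the decision coaching conversations should be kept to a minimum". It does not give the number of coaches, their caseloads or an expected ICC.

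The Decision coaching and Control group paragraphs and Implementation {16c} set the sequence. Intervention patients complete the Decisional Conflict Scale after coaching and before seeing the physician. Controls complete it before the consultation, without any coaching. Participant timeline {13} puts the decision aid and accompanying conversation at about 30–45 minutes.

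Sample size {14} uses a 10-point difference, and "the standard deviation was estimated to be 20.6 from the literature". It arrives at 71 per group by a two-group Mann-Whitney simulation "at a two-sided significance level of 5% with a power of 80" per cent. For the primary outcome, {20a} says "it will be analyzed by group comparisons (non-parametric comparison: van Elteren test) between the two study groups in which the stratification of randomization is considered". The stratification factor is preferred decision style, and {20b} names no other adjustment. Table 2, section 4, lists one sensitivity analysis, per protocol, and {20c} adds one for missing data. Neither concerns coaches.

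**The concern.** This is a partially nested design: patients are randomised individually, but in one arm they then share the person who delivers the intervention. The session works through the clarification of personal values, and the endpoint is values clarity, so a better or weaker coach can plausibly shift the scores of all of his or her patients together. Both the sample size and the primary test use patient-to-patient variation alone.

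The protocol recognises that coaching conversations may vary and takes a sensible design step against it. That step is an expectation about how large the variation will be, and none of the stated analyses checks it. If the trial is read as evidence that HELP coaching works whoever delivers it, the uncertainty that comes from having used only a few coaches is missing from the p-value and the interval.

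**Working it through.** **Reproducing the plan.** Inputs from {14}: difference 10, SD 20.6, two-sided 5%, power 80%. The normal-theory requirement for two means is 67 per arm. Before rounding, and multiplied by π/3 for the Mann-Whitney test under normality, it is 69.8, so 70. Direct simulation with independent normal scores (100,000 runs) gives 79.5% power at 70 per arm, 80.1% at 71, and 5.02% rejection under the null. Dropout: 71/0.80 = 88.75, so 89 per arm and 178 in total. The stated figures reproduce with independent patients, so they contain no allowance for coaches.

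**Assumptions not in the document.** k coaches with equal caseloads of 71/k; ICC ρ = share of intervention-arm variance lying between coaches; total SD held at 20.6 in both arms. For scale, ρ = 0.05 means a between-coach SD of 20.6 × √0.05 = 4.6 points.

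**False-positive rate for a zero average effect, coaches regarded as a sample.**
- Design effect in the intervention arm: DE = 1 + (71/k − 1)ρ.
- Only one arm is affected, so the variance of the difference is multiplied by f = (DE + 1)/2.
- Rejection rate of the test that ignores coaches: 2 × [1 − Φ(1.96/√f)].

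Example, k = 4 and ρ = 0.05: caseload 17.75; DE = 1 + 16.75 × 0.05 = 1.84; f = 1.42; rate = 2 × [1 − Φ(1.96/√1.42)] = 10.0%.

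| Coaches | ICC | DE | f | Formula | Simulated rank test (20,000 runs, no strata) |
|---|---|---|---|---|---|
| 4 | 0.01 | 1.17 | 1.08 | 6.0% | 5.9% |
| 4 | 0.02 | 1.33 | 1.17 | 7.0% | 7.0% |
| 4 | 0.05 | 1.84 | 1.42 | 10.0% | 9.5% |
| 4 | 0.10 | 2.68 | 1.84 | 14.8% | 14.6% |
| 6 | 0.05 | 1.54 | 1.27 | 8.2% | 8.1% |
| 10 | 0.01 | 1.06 | 1.03 | 5.4% | 5.4% |
| 10 | 0.02 | 1.12 | 1.06 | 5.7% | 5.5% |
| 2 | 0.05 | 2.73 | 1.86 | 15.1% | 14.4% |

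**Power of the planned test.** Simulated van Elteren test, three decision-style strata, 71 per arm, difference 10, 4 coaches: about 79–80% at ICC 0, 78% at 0.02, 76% at 0.05 and 73% at 0.10. The lowest value found was 70%, with 2 coaches at ICC 0.10.

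**Power of an analysis that respects the nesting.** With a normal critical value, the standard error without a coach effect is 20.6 × √[2/(71 × 3/π)] = 3.54. At k = 4 and ρ = 0.05, power = Φ(10/(3.54 × √1.42) − 1.96) = 66%. That is optimistic for few coaches. Comparing coach means with controls using Satterthwaite degrees of freedom gives about 57% in simulation. This loss belongs to the nested analysis, not to the planned test.

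**The case against.** Three objections carry weight.

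First, a reader might infer that the 5% level is lost whenever coaches could differ. The design does not support that. Randomisation is individual within decision-style strata, and the van Elteren test uses the same strata. If coaching changes nobody's score, coaches cannot differ in their effect on it, and the test keeps 5% whatever their number. The rates above need a different null: an average effect of zero over a wider set of coaches, some raising and some lowering scores. A rejection then reflects a real effect of the coaches who happened to be used. What is at issue is generalisation beyond them, in a trial run at one centre. This objection stands and limits the point.

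Second, a reader might infer that the trial is badly underpowered because 57% lies so far below 80%. That compares two different tests. For the test that the protocol specifies, the loss in the same scenario is about 3 points. This stands too.

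Third, the number of coaches and the ICC are unknown, and standardised training, a conversation guide, a neutral role and a single short session all favour a small ICC. An extra sensitivity model or a coach field may also sit in a fuller document, and silence here does not show that the coach went unrecorded. This lowers the weight of the point but does not remove it. The article itself fixes the sample size, the primary test and its only adjustment factor, and all of these rest on independence within the coached arm.

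**Conclusion.** The nesting is real and the stated analyses do not address it. The primary test is sound for the strict null and for the participating coaches. Its p-value and interval are too narrow only for a statement about HELP coaching in general, and only to the extent that coaches differ.

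The size cannot be fixed from the document. It runs from negligible (10 coaches, ICC 0.02 or less) to roughly a doubling of the nominal error rate (4 coaches, ICC 0.05), with larger values at ICC 0.10 or with 2 coaches. These figures assume normal scores and equal caseloads. The point is a cheap improvement that tests an assumption the plan relies on. It is no reason to change the primary test or the sample size.

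**What to change.** - Keep the van Elteren test as primary and leave N unchanged.
- Record the coach for every intervention patient. Recruitment was due to end around 31.01.2023, so the coach may have to be recovered from appointment records if it was not captured.
- In Table 2, section 4, add one sensitivity analysis of values clarity: a partially nested linear model with arm and decision style as fixed effects, a coach random effect in the intervention arm only, arm-specific residual variances, and Satterthwaite or Kenward-Roger degrees of freedom. Report the coach ICC and the mean score by coach.
- State in {14} that the 80% power assumes no coach effect.
- Fix in advance that, if the primary and nested results disagree, the conclusion is limited to the coaches who took part.

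The cost is one data field and one analysis, with no additional patients. The drawback is that with few coaches the nested interval will be wide. With only 2 coaches the model is unreliable, and results by coach should then be descriptive only.

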#### Physicians

To enable the integration of the decision aid in physician-patient consultations, a training course on the application of the decision aid in the context of everyday clinical practice at the Thoraxklinik Heidelberg was developed and conducted with the professionals involved in the decision-making process. In addition to important information and exercises on how to conduct conversations in the context of shared decision-making within the training, application materials (e.g., a manual) were provided for the professionals.

### Who will gather informed consent? {26a}

Research Assistants will introduce the trial to patients with the help of an information sheet. Patients have the opportunity to discuss the trial with the research assistant and to ask questions, before the research assistant will obtain written consent from patients willing to participate in the trial.

### Additional consent provisions for collection and use of participant data and biological specimens {26b}

Not applicable as no ancillary studies will be conducted.

## Interventions

### Explanation for the choice of comparators {6b}

Patients may feel better prepared and thus more able to participate actively in decisions concerning their treatment when they get a decision coaching and/or decision aid before the consultation takes place. Therefore, usual care, i.e. standard consultation with the physician without decision aid and/or decision coaching, was chosen as comparator. Patients without additional decisional support are expected to participate less in the consultation.

### Intervention description {11a}

Eligible patients will be randomized in equal proportions between the intervention group (i.e., decision coaching with decision aid) and the control group (i.e., usual care/standard consultation) according to the characteristic of preferred decision-making at baseline (expressions: physician should decide; patient would like to decide alone; patient and physician should decide together).

#### Intervention group

The intervention consists of the use of the decision aid, accompanied by a decision coaching session.

##### Decision aid

The decision aid HELP consists of a brochure for defining information and decision-making needs, including the patient’s personal values, as well as an overview of the most common forms of therapy. Both components are also available in digitalized form as a web app (htttps://awhelp.herokuappcom/#/).

The brochure entitled “What is important to me for my treatment?” includes questions on the patient’s information needs (e.g., information on the disease, treatment options, and side effects) and a section with questions on the patient’s decision-making behavior, i.e., how or with whom they want to make the treatment decision (alone, with the doctor, with relatives). The brochure ends with a clarification of the patient’s personal values (value clarification) and a section for open questions for the physician.

The second brochure entitled “Overview of common forms of therapy” includes information about the process, effect, duration and effort, side effects, and advantages vs. risks of common therapies, i.e., palliative therapy, chemotherapy, radiotherapy, immunotherapies, and targeted therapies.

